#### Statistical analysis

The study involves a series of quantitative outcomes and different types of hypotheses. Hypotheses about differences between patients treated with dynamic or static technique will be addressed by describing and visualizing the distribution of the corresponding variables in each patient group and by quantifying the group differences by the difference in mean values with 95% confidence intervals and p-values. Hypotheses concerning the association between two variables will be addressed by visualizing the joint distribution of variables in scatter plots and quantifying the association by partial correlations coefficients with 95% confidence intervals. Hypotheses concerning a change over time will be addressed by visualizing the distribution of individual differences and quantifying the change over time by the mean difference with 95% confidence intervals and p-values. Hypotheses concerning the association in change over time between two variables will be addressed by visualizing the joint distribution of differences in scatter plots and quantifying the association by correlations coefficients with 95% confidence intervals. In addition, the relation to baseline values will be examined. Patient characteristics will be tabulated for each patient group.

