## Methods/design

### Specific aims

The dynamic MPFL reconstruction is a muscle transfer procedure, and we assume that the function and timing of the gracilis muscle activity will change after dynamic MPFL reconstruction. We will compare longitudinal clinical and biomechanical outcomes (Table 1) between two major existing techniques: static reconstruction technique according to Schöttle et al. [20] and dynamic reconstruction technique according to Becher et al. [29].

**Table 1 Tab1:** Procedures summary

Project period	Pre-hospitalization/Screening	Hospitalisation	Follow-up				
Assessment	1	2	3	4	5	6	7
Time	Day 0	Length of stay	6 weeks ± 2 weeks	12 weeks ± 3 weeks	6 months ± 4 weeks	12 months ± 4 weeks	24 months ± 4 weeks
Diagnostics (X-Ray, MRI as indicated)	x						
Informed Consent (Surgery and study)	x						
In-/Exclusion Criteria	x						
Pre-op. Physical examination	x	x (Day 0)					
Data to be provided by the treating clinician							
Intervention (CHOP Code)		x (Day X_1_)					
Complications		x (Day 0-X_2_)	x	x	x	x	x
Physical examination	x	x	x	x	x	x	x
Data to be extracted from routine records							
Demographics		x (Day 0)					
Medical history and medication		x (Day 0)					
Radiographic parameters	x						
Length of stay		x (Day 0)					
Complications		x (Day X_2_)					
Data to be collected by the study nurse in cooperation with the patient							
Kujala, Tegner, Lysholm score, Banff-score		x (Day 0)	x	x	x	x	x
Patient satisfaction		x (Day X_2_)	x	x	x	x	x
End of rehabilitation/end of physiotherapy			x	x	x	x	x
Data to be collected at the Functional Biomechanics Laboratory in cooperation with the patient							
Isokinetic muscle strength	x					x	
Gait analysis	x					x	

#### Specific Aim 1

Compare the clinical outcome of dynamic and static MPFL reconstruction.

#### Hypothesis 1

Patients with dynamic MPFL reconstruction will report equal or better patient reported outcomes compared to patients with static MPFL reconstruction, as assessed with the Kujala score [35] (primary outcome), Banff-II-score [36], IKDC-2000 [36] and the EQ-5D-5L [37]. Patients with dynamic MPFL reconstruction will have comparable redislocation rates. The few studies published to date [29, 38] show good or better clinical results with the dynamic MPFL reconstruction.

#### Specific Aim 2

Evaluate and compare the biomechanical outcomes of dynamic and static MPFL reconstruction.

#### Hypothesis 2

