## Clinical trial protocol

Data of the patients will be collected pre- and postoperatively, and all patients will be in contact with the study staff for 2 years (Fig. 2). All patients fulfilling the inclusion criteria will be enrolled consecutively, thus avoiding selection bias. Participants will be followed up for 2 years with a total of five follow-ups at 6 weeks, 12 weeks, 6 months, 12 months and 24 months. Preoperative magnetic resonance imaging (MRI), upright radiographs, surgical reports and patient files will be evaluated. Patients who fulfil the inclusion criteria but refuse participation will be documented in a separate screening log.

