#### Sample size calculation

We based our sample size calculation on the primary outcome, the Kujala score. To date, no high-quality study (randomized trial) on the difference in change in Kujala score between dynamic and static MPFL reconstruction is available. However, in a prospective randomized control trial, Kang et al. [56] compared two different tensioning techniques for static MPFL reconstruction. They reported an effect size of 7.8 for the improvement in the Kujala score for both groups and a group difference in change in Kujala score of 1.9. Based on biomechanical considerations, we expect a larger improvement in patients stabilized using the dynamic MPFL reconstruction. Assuming a 3.8-point improvement in the Kujala score in patients with dynamic MPFL reconstruction compared to patients with static MPFL reconstruction, 54 patients (27 per group) are required to detect a significant difference in change in Kujala score between the two groups with 80% power at a significance level of 5%. We expect a dropout rate of about 10%, and will thus we will target a study cohort of 60 patients (30 per group).

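### The stated technique comparison is only a difference in means, so a late-visit Kujala comparison makes no stated use of leavers' earlier scores and can be biased if score-dependent leaving differs between arms

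*Protocol article*

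**What the plan says.** Under Specific aims, the protocol article announces that "We will compare longitudinal clinical and biomechanical outcomes". Table 1 in that section has a row for "Kujala, Tegner, Lysholm score, Banff-score" that is marked at Day 0 and at every follow-up. The Clinical trial protocol section confirms "a total of five follow-ups at 6 weeks, 12 weeks, 6 months, 12 months and 24 months".

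The Statistical analysis section sorts the hypotheses into types and gives a method for each. Differences between the techniques are addressed by description, plots and "by quantifying the group differences by the difference in mean values with 95% confidence intervals and p-values". Change over time is addressed through each patient's own difference between time points. On baseline it says only: "In addition, the relation to baseline values will be examined".

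Under Sample size calculation the article states: "We based our sample size calculation on the primary outcome, the Kujala score". The target is a 3.8-point difference in change, with 27 patients per group. On attrition it says "We expect a dropout rate of about 10" per cent, and the response is to recruit 60. No follow-up visit is named as primary.

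**The concern.** Six extra patients restore the number analysed. They do not restore the comparability of the arms if the patients who leave differ from those who stay, and differ in another way in each arm. A patient lost after the 12-month visit has up to four postoperative Kujala scores on file, and a difference in observed means at 24 months uses none of them.

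Loss that differs by arm is conceivable here. The Background describes persistent pain as a consequence of an over-tensioned static graft, and the Specific aims describe the dynamic technique as a muscle transfer, so the two may do badly in different ways. Blinding of patients does not prevent leaving that depends on how the knee feels. At stake is the primary outcome, in a trial whose first hypothesis is that the dynamic technique does equally well or better.

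**Working it through.** **Inputs from the article.** 27 per group, target 3.8 points, 80% power, 5% significance level, dropout about 10%, enrolment 60. The SD of the change score and the sidedness of the test are not stated.

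**1. Dropout step.** 54 / (1 − 0.10) = 60. The plan's figure is reproduced.

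**2. SD implied by 27 per group.** With the t distribution, two-sided, the detectable standardised difference is 0.777, so SD = 3.8 / 0.777 = 4.9. The normal approximation gives 3.8 / 0.762 = 4.98. A one-sided test would imply 5.5 to 5.6. The 7.8 that the article calls an effect size is not this SD: used as one, it requires 67 per group two-sided or 53 one-sided.

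**3. Standard error.** 4.9 × √(2/27) = 1.33 points.

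**4. Where bias comes from.** Suppose leaving depends on an earlier score that has correlation ρ with the late score. The bias of the observed-case difference is then

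bias = ρ × SD × (shift in the dynamic arm − shift in the static arm),

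where each shift is the standardised mean earlier score of those who stay minus that of everyone randomised to the arm. Equal shifts cancel. Bias needs a difference between arms, not merely leaving that depends on the score.

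**5. Simulation at SD 4.9.** Assumptions: 30 per arm, about 10% overall loss between 12 and 24 months, log-odds of leaving 1.2 per SD of the 12-month score, ρ from 0.5 to 0.8. Two patterns were tried: 20% leaving one arm and none the other, and about 11% leaving each arm in opposite directions. Together they give a bias of about 0.5 to 0.9 points, with the opposite-direction pattern at the upper end. A repeat with large samples gave the same picture, and a bias of about zero when both arms lost the same share by the same rule.

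**6. Second set of dropout rules.** Assumptions: SD 5, ρ 0.5 or 0.7, log-odds 1 or 2 per SD (2 only for opposite rules), true difference 3.8, overall loss 10%.

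| How leaving depends on the earlier score | Bias of observed-case difference |
|---|---|
| Not at all | about 0 |
| Same rule in both arms | −0.1 to −0.4 |
| In one arm only | −0.7 to +0.45 |
| Opposite rules in the two arms | −0.7 to −1.0 |

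Using the leavers' earlier scores gave about 3.8 in every row. The small negative bias under a common rule arises because, with a true benefit, the better arm loses fewer patients. With no true difference, the common rule gives zero bias by symmetry.

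**7. Scale.** 0.5 / 3.8 = 13% and 0.9 / 3.8 = 24% of the target; 0.9 / 1.33 = 0.7 standard errors.

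**8. Precision.** With random loss, using the 12-month score lowers the standard error by 0 to 3%. Power rises from about 80% with 27 completers per group to at most about 84%, and that only if all 30 per group were fully informative.

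**The case against.** The strongest reply is that a difference in means is an effect measure, not an estimator. A mixed model also reports one with a confidence interval, and a condensed article may leave the model and the treatment of missing visits to a fuller document. A reader might infer that the plan restricts the analysis to completers or discards leavers' scores. The article says neither. That reading is an inference: the sample size budgets leavers as contributing nothing, change is handled through individual differences that need both scores, and baseline is a side analysis. What remains is that the section does give a method for technique differences, and that method makes no stated use of the repeated scores.

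Four further objections stand and limit the point:

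- A leaver's scores still count in comparisons at the visits attended. Only later comparisons lose them, and no visit is fixed as the deciding one.
- It would be tempting to say that the comparison is biased whenever leaving depends on how the knee is doing. Steps 4 to 6 do not support that.
- An assumed SD of 10 gives biases of 1.0 to 1.8 points, but 27 per group would then have only about 28% power. That scenario does not match this plan and should not carry the argument.
- The likelihood estimate recovers the truth in the simulations by construction, because leaving was made to depend only on a recorded score. If patients leave after an unrecorded deterioration, that protection is lost.

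**Conclusion.** The point holds in limited form. The stated method fits poorly with a longitudinal comparison and expected dropout. On its natural reading, a late-visit Kujala difference can be off by about 0.5 to 0.9 points, or 13 to 24% of the target, if score-dependent leaving differs between arms. With weaker or stronger assumed rules the range is wider, roughly 0.2 to 1.0 points. The bias is at most about 0.4 points if both arms follow the same rule, and zero if loss is random.

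The figures rest on an SD that is implied and not stated, and on assumed correlations and dropout rules. The article gives no evidence that leaving will differ between arms, so this is an avoidable risk and not a demonstrated bias. It is worth changing because the data that reduce it are already being collected.

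**What to change.** Name the primary visit, and state for Kujala and the other repeated questionnaires:

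> The technique difference at the primary visit, with its 95% confidence interval, will be estimated from a likelihood-based linear mixed model for repeated measures including every randomised patient with at least one postoperative score. Fixed effects are technique, visit, technique-by-visit, baseline score, baseline-by-visit and centre. The within-patient covariance is unstructured, with a Kenward-Roger correction. If the model does not converge, a simpler covariance structure named in advance will be used.

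Keep the simple difference in means at each visit as description. With baseline as a covariate, the technique effect at a visit is the same for the score and for its change from baseline, so it matches the contrast used in the sample size.

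**Cost.** Analysis wording only, with no extra data. Five visits need 5 × 6 / 2 = 15 covariance parameters from 60 patients, hence the small-sample correction and the fallback. Five blocks of six give 30 codes per centre, so 60 patients fill two lists and centre then costs one degree of freedom. The model assumes that missingness is explained by observed scores, and patients with no postoperative score still drop out of it.

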### Participants

We will examine 60 patients undergoing isolated MPFL reconstruction due to patella dislocation. The patients will be randomly assigned to the procedure (static reconstruction technique according to Schöttle et al. [20] or dynamic reconstruction technique according to Becher et al. [29]) using an a priori generated list of codes assigned in five blocks of six codes per center generated with a block randomization generator (www.sealedenvelope.com). Patients and the staff collecting questionnaires or biomechanical data will be blinded to the surgical procedure.

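### The stated between-arm comparison leaves baseline Kujala and centre out of the treatment-effect estimate; it is valid, but adjusting for both would probably give a more precise answer from the same data

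*Protocol article*

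**What the plan says.** The Statistical analysis section sets one approach for hypotheses about differences between the dynamic and static groups: describe and plot the distributions, then summarise by "quantifying the group differences by the difference in mean values with 95% confidence intervals and p-values". It names no covariate and no centre term. Baseline is mentioned once, afterwards and separately: "In addition, the relation to baseline values will be examined".

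Three other places bear on this:

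- **Specific aims, Table 1.** The row "Kujala, Tegner, Lysholm score, Banff-score" is marked at Day 0 and at all five follow-ups, so a preoperative Kujala is available. Strength and gait are measured before surgery and at 12 months.
- **Participants.** The allocation codes are "assigned in five blocks of six codes per center", so centre is a design factor.
- **Sample size calculation.** The 54 evaluable patients are those needed to "detect a significant difference in change in Kujala score between the two groups". This suggests that the primary comparison is of change scores.

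**The concern.** In a randomised comparison with a preoperative value of the outcome, there are three usual estimators: the difference in follow-up means, the difference in mean change, and the difference adjusted for baseline by ANCOVA. All three are unbiased over randomisation. They differ in precision, and in what happens when the arms differ at baseline by chance. A follow-up difference carries part of the imbalance with it. A change-score difference over-corrects for it, through regression to the mean. ANCOVA removes the expected shift.

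The article's wording points to one of the first two. With 27 evaluable patients per arm, the precision given up could matter, and a chance imbalance could shift the estimate by a noticeable part of the 3.8-point target. Leaving out centre after blocking within it makes the standard error somewhat too large if centres differ.

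**Working it through.** **Inputs from the article.** Target difference 3.8 points, 5% significance level, 80% power, 27 per group (54), about 10% dropout, 60 recruited. The article gives no SD, no correlation between baseline and follow-up (rho) and no between-centre variance. It does not state sidedness; two-sided is assumed.

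**The plan's own figure.** The dropout step reproduces: 54/0.9 = 60. The 54 cannot be checked without an SD, so I solved backwards. With a two-sided t-test, 27 per group and 80% power for 3.8 points imply an SD of change of 4.89 (4.98 by the normal approximation), a standardised difference of 3.8/4.89 = 0.777. The 7.8 that the article calls an effect size does not serve as the SD: it would need 67 per group and give 43% power at 27. The power figures below therefore take the stated 80% as true.

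**ANCOVA against the change score.** Let k be the baseline SD divided by the follow-up SD. The variance ratio is

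(1 − rho²)/(k² + 1 − 2·rho·k).

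With equal variances (k = 1) this is (1 − rho²)/(2(1 − rho)) = (1 + rho)/2. Power uses a standardised difference of 0.777/sqrt((1+rho)/2) at 27 per arm, less one degree of freedom:

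| rho (assumed) | Variance ratio | CI width ratio | Power at 27 per arm | Per arm for 80% |
|---|---|---|---|---|
| 0.3 | 0.65 | 0.81 | 93.5% | 18 |
| 0.5 | 0.75 | 0.87 | 89.9% | 21 |
| 0.7 | 0.85 | 0.92 | 85.9% | 24 |

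**If variances are unequal.** Take rho = 0.5.

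- k = 0.5: 0.75/(0.25 + 1 − 0.5) = 1.00, so no gain.
- k = 1: 0.75/(1 + 1 − 1) = 0.75.
- k = 1.5: 0.75/(2.25 + 1 − 1.5) = 0.43, a larger gain.

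The ratio never exceeds 1, so in large samples ANCOVA is never less precise than the change score. The price is the degree of freedom.

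**If follow-up scores are compared instead.** The ratio is 1 − rho² = 0.91, 0.75 and 0.51 at rho 0.3, 0.5 and 0.7. Using 4.89 as the follow-up SD (a further assumption), power is 83.5%, 89.9% and 97.5%.

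**Chance imbalance.** The standard error of the baseline difference is sqrt(2/27) = 0.272 SD. At rho = 0.5 with equal variances, the SD of change equals the SD of the score, 4.89, so one standard error is 0.272 × 4.89 = 1.33 points. The expected shift is rho × 1.33 = 0.67 points in a follow-up difference, and (1 − rho) × 1.33 = 0.67 points, in the opposite direction, in a change-score difference. Against the target, 0.67/3.8 is about 17.5%.

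**Centre.** Five blocks of six make 30 codes per centre, so 60 patients would fill two lists; two centres is therefore an assumption. If centre explains 0, 5 or 10% of outcome variance, adding it alone gives 80.0%, 81.9% or 83.9% power.

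**The case against.** The best defence is that the section is a condensed template for many outcomes. A difference in mean values could be an adjusted one, and covariates are often left to a statistical analysis plan, which is not shown here. I find that reading strained. The same section specifies partial correlations for associations between variables, so it names adjustment where it intends it, and it presents baseline as an additional examination. An unseen plan may still add adjustment; the point concerns the estimator that the article states.

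Other objections stand and limit the point:

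- The sample size rests on change in Kujala, so baseline probably enters by subtraction. A reader might infer that baseline is ignored altogether and that the losses against raw follow-up scores apply to the primary outcome. The documents do not support that; the likelier comparison is ANCOVA against the change score.
- A reader might also infer that the planned analysis is biased or invalid. It is not. The shift from imbalance is conditional on the imbalance observed and averages to zero over randomisation.
- The (1+rho)/2 ratio needs equal variances, and the article gives no SD at either time. The power figures also start from an 80% that cannot be reproduced.
- Omitting centre leaves the estimate unbiased and the inference, if anything, conservative. No difference between centres is documented.
- One model cannot cover every outcome. Table 1 collects the scores up to 24 months but strength and gait only at 12; satisfaction has no preoperative value; running and drop landing depend on comfort and absence of pain, so some baselines may be missing.

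The asymmetry indices are bounded at zero, which calls for checking the model's fit. The same caution applies to a plain difference in means.

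**Conclusion.** The point holds as a loss of efficiency, worth correcting but not a threat to validity. The direction is secure: with 1:1 allocation, large-sample ANCOVA is at least as precise as either unadjusted comparison, apart from one or two degrees of freedom. The size is not secure. Under equal variances and rho between 0.3 and 0.7, variance falls by 15 to 35% against the change score. A true 80% power would become about 86 to 94%. With unequal variances the gain may be greater or close to nil. The centre term is minor, and worth nothing if centres do not differ. None of these inputs is in the article, so the figures show a range and are not a forecast.

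**What to change.** In the Statistical analysis section, state the primary estimate as the adjusted mean difference (95% confidence interval, p-value) from a linear model of Kujala at the primary follow-up time point on arm, baseline Kujala and centre, and name that time point in the sentence.

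Use the same form for secondary and biomechanical outcomes that have a preoperative value, each at its own follow-up time. Outcomes without one, such as satisfaction, take arm and centre only. Where a baseline is missing, for example because running or drop landing was not performed, keep the patient in the comparison by a simple pre-stated rule such as imputing the baseline mean over both arms.

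The cost is a few sentences and one or two degrees of freedom (one for baseline, one for centre if there are two centres), about 0.1 power point if a term explains nothing. No new data are needed. Fixing the model in advance also removes any later choice between adjusted and unadjusted results.

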**Discussion:**

The results of the study will clarify whether the reported surgery success for patella stabilization via dynamic MPFL reconstruction is due to muscle contraction or to the passive tenodesis effect combined with clinical outcome measures. With this study, we will provide much needed information on knee biomechanics after dynamic versus static MPFL reconstruction to provide evidence to support orthopedic surgeons in evidence-based decision-making in their quest for surgical techniques most favorable for their patients.

*Trial registration* The study protocol was registered at clinicaltrials.gov (NCT04849130). Registered 19 April 2021, https://clinicaltrials.gov/ct2/show/NCT04849130.

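### Associations between two changes over time are given plain correlations; if the arms are pooled, the arm difference mixes with the within-arm association, so adjust for randomised arm

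*Protocol article*

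**What the plan says.** All references are to the protocol article.

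- **Statistical analysis, two variables:** "quantifying the association by partial correlations coefficients with 95% confidence intervals". The variable partialled out is not named.
- **Statistical analysis, two changes over time:** "quantifying the association by correlations coefficients with 95% confidence intervals. In addition, the relation to baseline values will be examined". No adjustment variable is named, and the section does not say whether the coefficient is computed over both arms together or within each arm.
- **Statistical analysis, p-values:** they are planned for group differences ("quantifying the group differences by the difference in mean values with 95% confidence intervals and p-values") and for mean changes over time. The correlations get confidence intervals and scatter plots only.
- **Sample size calculation:** "we expect a larger improvement in patients stabilized using the dynamic MPFL reconstruction", with a planned difference of 3.8 points.
- **Hypothesis 2:** less asymmetry in strength and gait is expected with the dynamic technique.
- **Specific aims and Hypothesis 3:** gracilis function and timing are expected to change after the dynamic transfer.

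**The concern.** A correlation computed over two randomised arms together has two sources: the association among patients within an arm, and the separation of the arm means. The second vanishes only if treatment leaves at least one of the two variables unshifted. This protocol expects shifts in both the Kujala change and the biomechanical change.

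Suppose the expectations are right, so that Kujala change is larger and asymmetry falls more in the dynamic arm. The pooled correlation between the two changes is then negative even if, within each arm, a patient's change in asymmetry says nothing about that patient's change in Kujala score. A reader could take it to mean that patients whose gait became more symmetric improved more, when it only restates the two arm differences. If the arm shifts pull against a real within-arm association, pooling weakens it instead.

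At stake is the interpretation of secondary association analyses. The comparison of Kujala change between arms does not use these correlations.

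**Working it through.** **1. The plan's own figure.** The Sample size calculation states that "54 patients (27 per group) are required to detect a significant difference in change in Kujala score between the two groups", at 80% power and a 5% significance level. No SD of the Kujala change is given, so 27 per group cannot be reproduced. The figure of 7.8 cited there is called an effect size, not an SD; read as an SD, it would require 67 per group. The dropout step does reproduce: 54 / (1 − 0.10) = 60.

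**2. Standardised Kujala shift implied by the stated N.** Sidedness is not stated; two-sided is assumed.

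- Normal approximation: d = (1.960 + 0.842) × √(2/27) = 2.802 × 0.2722 = 0.76, so SD = 3.8 / 0.7625 = 4.98.
- t test: d = 0.78, SD = 4.89.
- One-sided, normal approximation: d = 0.68, SD = 5.62.

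The range 0.76–0.78 is used below. A larger SD would mean a smaller d and less distortion.

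**3. Pooled correlation with no within-arm association.** With 1:1 allocation, equal within-arm variances and arm shifts d₁ and d₂ in within-arm SD units:

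ρ = (d₁d₂/4) / √[(1 + d₁²/4)(1 + d₂²/4)]

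- d₁ = 0.76, d₂ = 0.5: 0.095 / √(1.1444 × 1.0625) = 0.086
- d₁ = 0.76, d₂ = 0.76: 0.1444 / 1.1444 = 0.126
- d₁ = 0.76, d₂ = 1.0: 0.19 / √(1.1444 × 1.25) = 0.159

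If one shift changes sign, so does ρ; its size is the same.

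**4. How often the 95% interval excludes zero.** Hand check for 0.76 on both, 54 patients, Fisher z: atanh(0.126) × √(54 − 3) = 0.127 × 7.14 = 0.91. The probability of exceeding ±1.96 is P(Z > 1.05) + P(Z < −2.87), about 0.15.

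Two simulations with independent normal changes within each arm and 27 per arm agree. One used d₁ = 0.76, Fisher z intervals and 100,000 trials per setting. The other used d₁ = 0.776, the t test for a correlation and 40,000 trials. The protocol gives no size for the biomechanical shift, so every value of d₂ is an assumption.

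| Kujala shift (SD) | Biomechanical shift (SD) | Plain pooled | Partial given arm |
|---|---|---|---|
| 0 | 0 | 5.0% | 5.0% |
| 0.76 | 0 | 5.0% | 5.0% |
| 0.76 | 0.2 | 5.7% | 5.0% |
| 0.38 | 0.38 | 5.7% | 5.0% |
| 0.5 | 0.5 | 7.0% | 5.2% |
| 0.76–0.78 | 0.5 | 9.4–9.6% | about 5% |
| 0.76–0.78 | 0.76–0.78 | 15.2–15.7% | about 5% |
| 0.76–0.78 | 1.0 | 21.3–21.5% | about 5% |
| 0.76–0.78 | 1.5 | 35.1–35.9% | about 5% |

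With 30 per arm (no dropout) and 0.76 SD on both, the plain figure is 16.1%.

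**The case against.** A reader might infer more than this: that the protocol plans pooled, unadjusted tests whose error rate is well above 5%, and that its main mechanistic conclusion rests on them. The document does not support that, for five reasons.

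- **Pooling is not stated.** Coefficients within each arm would carry no such distortion, and the text does not exclude them. Pooling is the natural reading because the section speaks of each patient group for the group comparisons but not for the correlations. It remains a reading.
- **No test is planned.** The correlations get intervals only. An interval that excludes zero is equivalent to a 5% test, but the protocol claims no error rate here.
- **No listed hypothesis names such an association.** Hypotheses 1 and 2 compare arms, and Hypothesis 3 concerns gracilis function after surgery. The Discussion part of the abstract promises to clarify whether success "is due to muscle contraction or to the passive tenodesis effect combined with clinical outcome measures", but it mentions no correlation. Aim 3 concerns the dynamic technique, so an analysis within that arm would be a natural choice.
- **The excess depends on the effects.** It is nil if either variable is unshifted and small at moderate shifts. Hypothesis 1 allows equal patient-reported outcomes, in which case Kujala change is unshifted.
- **The pooled coefficient is a legitimate marginal quantity.** It misleads only when read as an association among patients under the same treatment.

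It can also be said that covariates for secondary correlations belong in an analysis plan that is not shown. That is fair as to the missing covariate name. It does not dispose of the point: the article states a method for each kind of association and gives the plain coefficient to the changes, on which it expects treatment effects.

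**Conclusion.** The point holds in a limited form. As worded, change-with-change associations get a plain correlation while two-variable associations get a partial one, and arm appears in neither. If the arms are pooled and treatment shifts both changes, the interval for a truly absent within-arm association excludes zero in roughly 9–21% of trials, for an assumed biomechanical shift of 0.5–1.0 SD alongside the Kujala shift implied by the stated sample size. The excess shrinks to almost nothing for smaller shifts and disappears if either variable is unshifted.

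These figures assume 27 evaluable patients per arm for both variables, normal changes with equal within-arm variances, a two-sided sample size calculation, and interest in the within-arm association. Minor priority: only secondary analyses are touched.

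**What to change.** In the Statistical analysis section, replace the rule for two changes over time with wording such as: *Associations between two changes will be estimated by partial correlation given randomised arm, with 95% confidence intervals; scatter plots will mark arm, and coefficients within each arm will be reported descriptively.* In the preceding rule for two variables, name the variables partialled out and include arm among them.

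The within-arm coefficients matter because the association may differ between techniques: one harvests the gracilis tendon as a free graft, the other leaves it attached to its muscle. The adjusted coefficient assumes a common within-arm association, and this should be said when it is reported.

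Cost: that assumption, one degree of freedom and a few lines of text. No new data or patients are needed.
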